### Inclusion criteria

Participant is an inpatient at either UHBFT or HEFT.Participant is willing and able to give informed consent to participate in the study.Men or women, aged 18 years or more.Patient is registered with a general practitioner (GP) in the two main Clinical Commissioning Groups (CCGs—clinically led groups that include all GPs in their geographical area) served by UHBFT and HEFT (Birmingham South Central CCG and Birmingham Crosscity CCG). Clinical Commissioning Groups were set up in April 2013 arising as part of the reforms set out in the Health and Social Care Act 2012 and replaced primary care trusts.^27^

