### Study process

The study process is laid out in figure 1.
Hospital electronic records are automatically searched for current inpatients who fulfil the study entry criteria. Patients who are under local renal follow-up or have attended a renal clinic in the preceding 12 months or who are not registered with a GP in the two CCGs involved are excluded at this stage.Clinical staff responsible for the care of identified patients are approached to ensure they are appropriate for the study.The research team approaches suitable patients. Where possible an introduction will be made by a member of the clinical team known to the patient. If there is any doubt about the participant's ability to give informed consent, they are excluded.The researcher verbally explains the study and answers any questions the potential participant may have. The voluntary nature of participation and the ability to withdraw at any time is emphasised. As part of the consent process the patient is also asked to consent to the use of information held by the NHS and records maintained by the Health and Social Care Information Centre (HSCIC).^28^ The patient is given as much time as needed to think through their participation. After a suitable period, the patient is consented to participate in the study. Before consent, the researcher confirms with the participant that they have understood the patient information sheet.During this visit, the patient and a member of the study team jointly fill in a questionnaire including demographic details, usual GP, lifestyle factors, kidney disease diagnosis and admission medication.Data from biochemistry and haematology laboratory investigations are electronically collected including creatinine, estimated glomerular filtration rate, urea, albumin, haemoglobin, sodium, potassium, bicarbonate, phosphate, parathyroid hormone and cholesterol.A letter is sent to the GP with a photocopy of the consent form. The GP surgery is asked to insert a Read code into the patient's electronic health record. This will be to register within the GP database that the patient has consented to be a part of the study and enables subsequent extraction of preadmission data based on the QOF and prescribed medication records. Once the study has ended or the patient withdraws from the study, a second Read code will be sent to the GP that will prevent any further data extractions. The UK Terminology Centre has provided these Read codes.Preconstructed software already installed will automatically migrate the prespecified data to the Department of Informatics at UHBFT. All data will be transferred within the NHS N3 Network and held in a secure NHS hospital environment with strict restrictions on access and data reuse agreements.

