### Quality and Outcomes Framework (QOF)

This is a system for the performance management and payment of GPs in the NHS. It was introduced as part of the new general medical services contract in April 2004.^29^ Multiple clinical conditions are featured (see table 1) and it is a requirement for GPs to keep a database of all patients diagnosed. One example is CKD, where GPs are required to record all patients with an estimated glomerular filtration rate of less than 60 mL/min/1.73 m^2^ (stage 3 CKD or worse) on a practice register. This CKD record contains details of most patients labelled with CKD in the UK.^30^

**Table 1 BMJOPEN2014006987TB1:** Quality and Outcomes Framework (QOF) chronic disease domains

QOF domain	Point for analysis
Chronic kidney disease (CKD)	Is the patient on the CKD register?
	If so, was the last BP reading (in the preceding 12 months) 140/85 mm Hg or less?
	If so, what was the last ACR (or PCR) in the preceding 12 months?
Atrial fibrillation (AF)	Is the patient on the AF register?
	If so, what is their CHADS2 score?
	Is the patient treated with anticoagulation drug therapy or antiplatelet therapy?
Secondary prevention of coronary heart disease (CHD)	Is the patient on the CHD register?
	If so, what was the latest BP (within 12 months)?
	If so, what was the last measured cholesterol (within 12 months)?
	If so, has the patient received influenza vaccination in the previous 12 months?
	If so, is the patient on aspirin, alternative antiplatelet agent or oral anticoagulant?
Heart failure (HF)	Is the patient on the HF register?
	If so, is the patient currently treated with an ACE-I or ARB?
	If on ACE-I or ARB are they also treated with a β-blocker?
Hypertension (HYP)	Is the patient on the hypertension register?
	If so, has the BP measured in the preceding 9 months been less than 150/90 mm Hg?
Peripheral arterial disease (PAD)	Is the patient on the PAD register?
	If so, has the BP in the preceding 12 months been 150/90 mm Hg or less?
	If so, has the total cholesterol measured in the preceding 12 months been 5 mmol/L or less?
	If so, is the patient taking aspirin or an alternative antiplatelet agent?
Stroke and transient ischaemic attack (STIA)	Is the patient on the STIA register?
	If so, is the last BP reading measured in the preceding 12 months 150/90 mm Hg or less?
	If so, what was the last measured cholesterol (within 12 months)?
	If so, was the last measured cholesterol (within 12 months) less than 5 mmol/L?

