### Secondary outcomes

Hospital readmission rates for any cardiovascular event (including acute myocardial infarction, angina, coronary artery bypass graft surgery, percutaneous coronary intervention, peripheral arterial disease, revascularisation or stroke) in patients with and without CKD.All-cause and cardiovascular mortality in patients with and without CKD.Treatment received before, during and after admission to hospital with a cardiovascular event by patients with and without CKD.The risk: benefit ratio for primary and secondary prevention of cardiovascular disease in patients with and without CKD.Attainment of standards in chronic disease management in patients with and without CKD.Rates, severity and risk factors for acute kidney injury in patients with and without CKD.The proportion of patients with biochemical evidence of CKD not classified so by the GP.All primary and secondary outcomes will be analysed separately to investigate the influence of age, sex, ethnicity, socioeconomic status, deprivation score and concurrent comorbidities (including diabetes mellitus) on outcomes, treatment and classifications. Determination of socioeconomic status will be based on the Index of Multiple Deprivation model calculated at the local level.^34^

In the ACQUATIK study patients with renal disease under secondary care nephrology follow-up have been excluded. Therefore, the majority of diagnoses coded within HES and primary care databases will include common systemic conditions such as hypertension and diabetes mellitus as the aetiology of CKD, rather than primary renal glomerulonephritides which would invariably be under secondary care follow-up in the UK. Conditions such as diabetes mellitus will also be present in the non-CKD group and will form part of the prespecified analysis of comorbidities during data analysis.

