## Analyses

Normally distributed continuous data will be presented as mean±SD with comparisons made using Student's t test or one-way analysis of variance. Non-normally distributed data will be presented as median (IQR) and analysed using the Kruskal-Wallis test. Categorical data will be presented as count (percentage) and analysed using the χ^2^ test. In multivariable analyses, variables found to be significantly associated with the outcome under investigation in the univariable analyses will be used. Logistic regression analysis will be used to assess the relationship between outcomes and parameters under investigation and the results expressed as an OR with 95% CIs. Time-to-event data analysis will be performed using the Cox proportional hazards model and the results expressed as HR with 95% CIs.

Standard methods will be used to handle missing data after being assessed for extent and as to whether this is due to random missingness and/or censoring.^37^
^38^

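### The CI for the proportion with GP-unclassified CKD, and CIs for area-deprivation effects on GP-recorded outcomes, should allow for correlation within GP practice

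*Protocol article*

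**What the plan says.** Two of the secondary outcomes depend on what general practices record and do: "The proportion of patients with biochemical evidence of CKD not classified so by the GP" and "Attainment of standards in chronic disease management in patients with and without CKD". The same section says that all outcomes will also be examined for the influence of age, sex, ethnicity, socioeconomic status, deprivation and comorbidity.

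The section Quality and Outcomes Framework (QOF) describes the source of both. On the framework itself: "This is a system for the performance management and payment of GPs in the NHS". On CKD, for which each practice keeps its own register: "GPs are required to record all patients with an estimated glomerular filtration rate of less than 60 mL/min/1.73 m^2^ (stage 3 CKD or worse) on" that register. Under Inclusion criteria: "Patient is registered with a general practitioner (GP) in the two main Clinical Commissioning Groups". With at least 4000 patients drawn from two such groups, several patients per practice are to be expected.

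The Analyses section covers all outcomes in one generic list: "Categorical data will be presented as count (percentage) and analysed using the χ^2^ test", then logistic regression reported as odds ratios with 95% CIs, and Cox models for times to event. No practice term, random effect, GEE or robust standard error is named.

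The information needed is collected. At recruitment (Study process), patient and researcher complete "a questionnaire including demographic details, usual GP, lifestyle factors, kidney disease diagnosis and admission medication", and the GP surgery is then contacted so that its records can be extracted.

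**The concern.** Coding of CKD can differ between practices, and that variation is part of what the unclassified-CKD outcome measures. Independence between patients is therefore least plausible for this outcome. The usual binomial CI and the usual logistic model treat 20 patients from one practice as 20 separate pieces of information. If patients of a practice are positively correlated, they carry less.

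Two results are exposed. One is the single proportion with unclassified CKD. The other is the effect, on GP-recorded outcomes, of a predictor that patients of one practice tend to share; area deprivation is the obvious case, because patients of a practice tend to live near each other. A statement about how much CKD goes unrecorded, or about a social gradient in recording or attainment, could then carry more certainty than the data support.

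**Working it through.** **The plan's own figures.** The document states no precision or power for these secondary outcomes. Its only calculation (Number of patients) concerns the primary readmission rate. It reproduces with a log-rate comparison, 40% CKD, 2 years per patient and two-sided 5% (the last is assumed):

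- N = 2000: expected readmissions 800 × 2 × 0.116 = 185.6 and 1200 × 2 × 0.082 = 196.8; z = ln(116/82) / √(1/185.6 + 1/196.8) = 3.39; power 92.4%, against 92% stated.
- N = 4000: 1600 × 2 × 0.072 = 230.4 and 2400 × 2 × 0.056 = 268.8; z = ln(72/56) / √(1/230.4 + 1/268.8) = 2.80; power 79.9%, against 80% stated.

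That calculation does not bear on the present point.

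**Inputs for the proportion.** From the document: 4000 patients, about 40% with CKD, so 4000 × 0.40 = 1600. Assumed: 80 to 160 practices of equal size, so m = 1600/160 = 10 to 1600/80 = 20 CKD patients each, and ICC 0.02 to 0.10. For illustration the true proportion is set at 0.30.

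**Formulas.** Design effect D = 1 + (m − 1) × ICC. The CI should be √D times as wide. Actual coverage of a nominal 95% CI = 2Φ(1.96/√D) − 1. The unadjusted half-width at 0.30 is 1.96 × √(0.30 × 0.70/1600) = 2.25 percentage points.

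| m | ICC | D | √D | Coverage | Half-width needed (points) |
|---|---|---|---|---|---|
| 10 | 0.02 | 1.18 | 1.09 | 93% | 2.44 |
| 20 | 0.05 | 1.95 | 1.40 | 84% | 3.14 |
| 20 | 0.10 | 2.90 | 1.70 | 75% | 3.82 |

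**Wider assumptions.** With 50 to 200 equal practices (m = 32 to 8) and ICC 0.01 to 0.10, D runs from 1 + 7 × 0.01 = 1.07 to 1 + 31 × 0.10 = 4.10, and coverage from 94% to 67%.

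**Simulation of the unadjusted analysis.** Setup: 4000 patients; 50, 100 or 200 practices; a normal practice effect on the log-odds scale with ICC 0.01 to 0.10 on that scale; proportion about 0.30; 3000 runs per setting. Results:

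- CI for the proportion in about 1600 patients: coverage from 95% (200 practices, ICC 0.01) down to 73% (50 practices, ICC 0.10).
- Predictor constant within practice: type I error 6% to 44% at a nominal 5%.
- CKD versus non-CKD, with both groups in every practice and the CKD share not varying between practices: type I error 4.3% to 6.0%, which is about nominal.

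The third line separates the comparison that is safe from the two results that are exposed.

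**The case against.** **The document is silent rather than wrong.** The Analyses section is a short list in a condensed article. It does not say that patients will be treated as independent, and logistic regression with an odds ratio and CI is compatible with a random effect or robust errors. A full protocol or SAP may add this. That stands, and it limits the weight of the point. It does not remove it, because specific methods are named for all outcomes and, followed as written, they carry no practice term.

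**The CKD comparison is safe.** A reader might infer that the CIs for both GP-related outcomes are wrong. The documents do not support that. Attainment is compared between patients with and without CKD, who occur in the same practices, and the simulated error there is about nominal. Many QOF standards also rest on patient measurements such as blood pressure, cholesterol and HbA1c, so attainment is not purely a practice behaviour. For standards assessed register by register the clusters are smaller: if 10% of 4000 patients were on a register (an assumption), 400 over 80 to 160 practices gives 2.5 to 5 each and D of 1.03 to 1.40 for ICC 0.02 to 0.10. Nor does the chi-square test by itself yield a CI.

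**Deprivation is not a practice-level variable.** It comes from the patient's area of residence (a postcode-based index under Hospital Episode Statistics, a local-level index under Secondary outcomes) and can vary within a practice. The 6% to 44% error rate is therefore an upper case for deprivation. Ethnicity is recorded per patient, and inflation there too depends on how alike patients of a practice are.

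**Patients are sampled individually, not by practice.** If the target were only the practices that took part, the unadjusted CI for the proportion would be much less open to objection. The concern applies when the result is generalised beyond them. The article presents generalisability as a strength of the study, so that reading is a natural one.

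**Conclusion.** The point holds in a limited form. For the proportion with unclassified CKD, and for effects on GP-recorded outcomes of predictors that are similar within practice, the named methods make no allowance for practice, and CIs can be too narrow when results are generalised beyond the participating practices. Under 10 to 20 CKD patients per practice and ICC 0.02 to 0.10, coverage of a nominal 95% CI for the proportion is about 93% at best and 75% at worst. Both inputs are assumptions: with many practices and a very low ICC the effect is negligible, and with few practices and a high ICC it is serious. The document does not allow a choice within that range.

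It would be going too far to conclude that the study's secondary CIs are wrong in general. The comparison of attainment by CKD status is not materially affected, provided the CKD share does not vary much between practices, and the stated power for the primary outcome reproduces. This is a cheap improvement to some secondary analyses and does not threaten the study's main conclusion.

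**What to change.** Add one sentence to the analysis text: for GP-recorded outcomes (register classification, QOF attainment, GP prescribing), logistic regression will be fitted with GEE or cluster-robust standard errors by GP practice, and the CI for the proportion with unclassified CKD will be taken from the same marginal model.

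A marginal approach is preferable here because the quantity of interest is an overall proportion, which a random-intercept model does not give directly. Reporting the number of contributing practices and the estimated ICC would show readers how much the adjustment mattered.

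The cost is that some CIs become wider. No new data are needed, since the usual GP is already recorded at recruitment; each GP only has to be mapped to a practice.

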### Follow-up period and study end

The patient enrolment period is 2 years. Patients will be followed until death, withdrawal from the study, or for a maximum of 4 years, whatever comes first. For patients who died during follow-up, information about the causes of death will be collected. For patients who wish to stop participation in the study, the reason for withdrawal will be registered. The end of the study will be defined as the end of long-term follow-up 2 years after the last patient was recruited into the study. The data generated from this study will be held in a secure, anonymised database for 2 years after the study ends. The database will then be archived for a total of 10 years as per sponsor guidelines after the study ends to protect the integrity and auditability of the research. However, given the likelihood that this data will be of great value for future research the Chief Investigator will be applying for permission to maintain the database, under the relevant conditions, to the appropriate regulatory bodies.

### Number of patients

A minimum of 4000 patients will be recruited into the study. The sample size calculations were based on the following information. Approximately 40% of patients admitted to hospital will have evidence of CKD (data from 4 years of emergency admissions to Queen Elizabeth Hospital). This is consistent with published international data.^36^ From US Medicare data,^7^ patients without CKD aged 66 and over have a readmission rate of 82 per 1000-patient years whereas patients with CKD have a readmission rate of 116 per 1000-patient years. From US Marketscan data^7^ patients without CKD aged 50 to 64 have a readmission rate of 56 per 1000-patient years whereas patients with CKD have a readmission rate of 72 per 1000-patient years. Therefore, in a best case scenario, patients admitted to hospital in Birmingham have annual readmission rates similar to US Medicare data. To detect a difference of 34 (116–82) readmissions per 1000 patient-years with 92% power would require a sample size of 2000 with an average of 2 years follow-up. In a worst case scenario, patients admitted to hospital in Birmingham have annual readmission rates similar to US Marketscan data. To detect a difference of 16 (72–56) readmissions per 1000 patient-years with 80% power would require a sample size of 4000 with an average of 2 years follow-up.

## Analyses

Normally distributed continuous data will be presented as mean±SD with comparisons made using Student's t test or one-way analysis of variance. Non-normally distributed data will be presented as median (IQR) and analysed using the Kruskal-Wallis test. Categorical data will be presented as count (percentage) and analysed using the χ^2^ test. In multivariable analyses, variables found to be significantly associated with the outcome under investigation in the univariable analyses will be used. Logistic regression analysis will be used to assess the relationship between outcomes and parameters under investigation and the results expressed as an OR with 95% CIs. Time-to-event data analysis will be performed using the Cox proportional hazards model and the results expressed as HR with 95% CIs.

Standard methods will be used to handle missing data after being assessed for extent and as to whether this is due to random missingness and/or censoring.^37^
^38^

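### Continuous data are assigned to pooled-variance tests although the groups are natural and unequal in size; if variances also differ the 5% level is not held, and Welch's versions would avoid this at almost no cost

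*Protocol article*

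**What the plan says.** The Analyses section of the protocol article divides continuous data by distribution. Normally distributed variables are summarised by mean and SD, with "comparisons made using Student's t test or one-way analysis of variance". The rest go another way: "Non-normally distributed data will be presented as median (IQR) and analysed using the Kruskal-Wallis test". The section mentions neither a check of equal variances nor an unequal-variance version of the t test or ANOVA. It attaches 95% confidence intervals to odds ratios from logistic regression and to hazard ratios from Cox models, and to nothing else. It also says that variables significant in univariable analyses enter the multivariable models, without naming the univariable test.

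On group sizes, Number of patients states "Approximately 40% of patients admitted to hospital will have evidence of CKD" and "A minimum of 4000 patients will be recruited into the study". That gives about 1600 patients with CKD and 2400 without. No SD of any continuous variable appears in the article.

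Some of the data are continuous. In Table 1, for instance, the coronary heart disease domain asks for a blood pressure value: "If so, what was the latest BP (within 12 months". The laboratory results collected at the index admission are also continuous.

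**The concern.** Student's t test and classical one-way ANOVA estimate one common variance. When group sizes differ, that pooled estimate is weighted towards the larger group. If the smaller group is the more variable one, the standard error of the difference is too small and false positives rise. If it is the less variable one, the standard error is too large and real differences are missed.

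Randomised groups share a variance under the null hypothesis of no effect. Groups defined by disease, ethnicity or comorbidity carry no such guarantee. CKD is defined partly by a filtration rate below a cut-off and is far more common at older ages, while the study admits anyone aged 18 or over, so different spreads are plausible.

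At stake are the p-values for secondary and descriptive comparisons of continuous variables. If the same tests are used to screen variables, the set of covariates in the logistic and Cox models could change too.

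**Working it through.** **1. The plan's own figures.** The article's powers are for readmission rates: "To detect a difference of 34 (116–82) readmissions per 1000 patient-years with 92% power would require a sample size of 2000" and "To detect a difference of 16 (72–56) readmissions per 1000 patient-years with 80% power would require a sample size of 4000", each with an average of 2 years of follow-up. Take two Poisson rates, a 40:60 split and two-sided 5% (alpha is not stated, so this is an assumption), and test the log rate ratio.

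- N = 2000 (800 and 1200): expected events 0.116 × 800 × 2 = 185.6 and 0.082 × 1200 × 2 = 196.8. SE = √(1/185.6 + 1/196.8) = 0.1023. ln(116/82) = 0.3469. z = 3.390, and Φ(3.390 − 1.96) = 92.4%, against 92% stated.
- N = 4000 (1600 and 2400): expected events 230.4 and 268.8. SE = 0.0898. ln(72/56) = 0.2513. z = 2.799, and Φ(2.799 − 1.96) = 79.9%, against 80% stated.

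Both reproduce. Neither uses a t test, so the point made here leaves them unchanged.

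**2. True size of the pooled t test.** Let p be the share of the smaller group and k its SD divided by that of the larger group. Up to a common factor:

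- pooled variance of the difference: (p·k² + 1 − p) × (1/p + 1/(1 − p))
- true variance of the difference: k²/p + 1/(1 − p)
- true type I error ≈ 2 × [1 − Φ(1.96 × √(pooled/true))]

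The share p = 0.40 comes from Number of patients. Every value of k is an assumption.

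Worked case, p = 0.40 and k = 1.5: pooled = (0.4 × 2.25 + 0.6) × 4.1667 = 6.25. True = 2.25/0.4 + 1/0.6 = 7.2917. √(6.25/7.2917) = 0.9258. 1.96 × 0.9258 = 1.815. Two-sided tail = 7.0%.

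Simulation at 1600 v 2400, with 2,000,000 data sets per ratio, agrees with the formula:

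| SD ratio, CKD/non-CKD (assumed) | Student, formula | Student, simulated | Welch, simulated |
|---|---|---|---|
| 0.5 | 2.7% | 2.7% | 5.0% |
| 0.8 | 4.1% | 4.1% | 5.0% |
| 1 | 5.0% | 5.0% | 5.0% |
| 1.25 | 6.1% | 6.0% | 5.0% |
| 1.5 | 7.0% | 7.0% | 5.0% |
| 2 | 8.2% | 8.2% | 5.0% |

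**3. Does sample size help?** At 800 v 1200 and k = 1.5 the calculated size is 6.9%; at 1600 v 2400 it is 7.0%. The error depends on the size ratio and the SD ratio, not on N. At 2000 v 2000 it stays at 5.0% for every k tried.

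**4. More lopsided groups.** With an assumed 15:85 split the same formula gives 8.4% at k = 1.2 and 13.7% at k = 1.5, and 2.6% and 1.0% at the inverse ratios. For one-way ANOVA with assumed groups of 2800, 600, 400 and 200, simulation gives 5.0% with equal SDs, 16.8% if the three smaller groups have 1.5 times the SD, and 0.5% if the largest group does. The article gives none of these splits, so they show direction and scale only.

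**5. Cost of switching.** With equal SDs at 1600 v 2400, Welch's test has a critical value of 1.9607 against 1.9606 for Student's.

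**The case against.** The strongest reply is that half of the condition for harm is missing from the article. Unequal size does nothing by itself, no SD is reported, and nothing says that variances differ. That stands: the point is conditional. With an SD ratio of 1.1 or its inverse at 40:60, the size is only about 5.4% or 4.6%.

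It can also be said that this is a generic descriptive sentence in a condensed article, with variance checks left to an analysis plan that is not shown. That explains the lack of detail. But the article does name specific tests, and a better-behaved version of each exists.

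A reader might infer more than the text supports:

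- **That confidence intervals are wrong.** The planned intervals are for odds ratios and hazard ratios, and neither comes from a t test or ANOVA. No interval for a mean difference is specified.
- **That the attainment outcome is affected throughout.** Most blood pressure, cholesterol and HbA1c items in Table 1 are thresholds, which are categorical. Only a few are recorded as values.
- **That variable selection is affected.** The screening test is not named. Univariable logistic or Cox models fit the wording equally well.
- **That the 15:85 figures describe this study.** They would require a t test by readmission status, which the article does not specify. Weighting the assumed rates 40:60 gives 12% to 17% readmitted at 2 years. At about 3 years, within the planned 2 to 4, it is 17% to 25%. At 25:75 the error would be 7.3% and 10.7% for SD ratios of 1.2 and 1.5.

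Nor do equal group sizes fully protect ANOVA. With 800 per group, simulation gave 5.5% for SDs of 1, 1, 1 and 1.5. This is a reason to prefer Welch's ANOVA, not evidence of a fault in this study.

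**Conclusion.** The point holds as a minor one, in conditional form. The article assigns normally distributed continuous data to tests that pool variances, and its own CKD share makes the main groups unequal. If variances differ as well, the nominal 5% is not held, the direction depends on which group is more variable, and recruiting more patients does not help. For the CKD comparison the departure is modest at plausible SD ratios: about 4.1% to 6.0% for 0.8 to 1.25. It reaches 7.0% if the CKD group's SD is 1.5 times the other, and can be larger in more lopsided subgroups. These figures rest on assumed SD ratios and a two-sided 5% level.

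The reach is limited to secondary and descriptive comparisons of continuous variables, and to model building only if these tests are the univariable screen. The primary outcome is a readmission rate, the sample size rests on rates, and the odds and hazard ratio intervals come from other models. None of them is affected.

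**What to change.** In the Analyses section, where the text now reads "comparisons made using Student's t test or one-way analysis of variance", name Welch's unequal-variance t test for two groups and Welch's ANOVA for more than two. A linear model with heteroscedasticity-robust standard errors would serve equally well. Do not make the choice depend on a preliminary test of equal variances; use the unequal-variance version throughout. If mean differences are later reported with confidence intervals, take these from the same method.

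The cost is one sentence. The methods are standard in statistical software, the loss when variances are equal is negligible, and the sample size and stated powers do not change.
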